### Secondary outcomes

2.13

The secondary outcome indicators are the patient's best corrected visual acuity, naked vision, axial length, corneal curvature, and TCM syndrome scores before treatment, 1, 2, and 3 months after treatment, and at follow-up for 6 months, September, and 12 months.

### Safety evaluation

2.14

Clinical AEs will be recorded throughout the study. According to previous RCTs, the acupuncture may cause pain, bleeding, hematoma formation, fainting, severe pain, and local infection or other severe discomforts. Any unexpected symptoms or signs during the treatment must be documented regardless of their relation to the study intervention. All details of related and unexpected AEs, such as time of occurrence, severity of AE, and suspected causes, will be recorded on CRFs. Participants with mild and moderate AEs will receive symptomatic treatment and will be closely followed up by the research team. Severe AEs will be reported to the Research Ethics Committee within 48 hours.

Blood, urine, routine stool, liver function (Alanine aminotransferase, ALT, Aspartate aminotransferase, AST), renal function (Blood urea nitrogen, BUN, Serum creatinine concentration, SCr), and electrocardiogram will also be examined before treatment, at 1 month, 2 months and at the end of treatment.

### Data management and quality control

2.15

All participants are assessed at the first, second, third, sixth, ninth, and twelfth months after recruitment. A well-trained assessor, who is blinded to the treatment assignment, will collect clinical data using CRF files at each visit. Another 2 pre-trained data managers will verify and cross-check the CRFs, for the sake of ensuring reliability and accuracy of the data. If there are any queries in the CRFs, the results will be sent to the third investigator for resolution. Data managers will also be responsible for administration, coordination, and monitoring (including Excel spread sheet-set up, data entry, coding, and query management). Any incomplete data will be coded as unknown, missing, or not applicable, and all data will be anonymously extracted to keep the identities of patients confidential. Results of the analysis must not be released with individual identification of the subject until the Excel spread sheet is closed.

### Statistical analyses

2.16

Data analyses will be processed with SPSS 22.0 (SPSS Inc., Chicago, IL) and supervised by a skilled statistician blinded to group allocation.

The Full Analysis Set (FAS) is for all participants who have been randomized in terms of the intention-to-treat (ITT), and the per-protocol analysis set (PPS) and is for the individuals who complete the trial and do not have significant protocol violations. On the basis of rule of the last-observation-carried-forward, missing values will be imputed. In order to evaluate therapeutic effect and safety, the FAS and PPS will be used simultaneously.

Categorical data, such as gender and medical history, will be tabulated with frequencies or percentages; and continuous data, such as age and disease course, will be reported as mean ± standard deviation (SD), or median. For the baseline variables, sociodemographic data and other basic indicators will be carried out using analysis of variance (ANOVA) and χ^2^. To compare variables before and after treatment in the same group, a paired *t* test will be used. Repeated-measures ANOVA will be used to compare the intergroup differences among the 3 groups. Tests of ITT between the acupuncture with the deqi group and acupuncture without the deqi group arms and between the acupuncture withou the deqi group and waiting-list group arms with respect to the change will based on time-intervention interactions in the mixed-effect models. A *P* value of less than .05 (2-sided) indicates a statistically significant difference, with 95% confidence intervals.

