## Introduction

1

Myopia is the most common cause of avoidable visual impairment worldwide.^[1,2]^ Young academics in South-East Asia now face a frequency of up to 95.5% of myopia,^[3]^ accompanied by a high prevalence of high myopia (10–20%).^[4]^ In 2000, there were 1406 million myopia patients and 163 million high myopia patients, and it is predicted that by 2050, there will be 4758 million myopia patients (49.8% of the world population).^[5]^ Myopia brings further vision challenges, as high myopia increases the risk of pathologic ocular changes such as cataract, glaucoma, retinal detachment, myopic macular degeneration, and myopic choroidal neovascularization, all of which can cause irreversible vision loss.^[6,7]^ The global potential productivity loss associated with the burden of vision impairment was estimated at US$244 billion from uncorrected myopia and US$6 billion from myopic macular degeneration.^[8]^

The multifactorial mechanism of the increased prevalence of myopia is not fully understood. Several theories have been proposed to explain the recent increase and its earlier onset in children, including genetic markers,^[9,10]^ increased near work,^[11]^ and less time spent outdoors.^[12,13]^ There has been an increase in efforts to slow the progression of myopia, and a variety of treatment methods have been recommended for the management of myopia. Conventional therapies included single vision spectacle lenses, multifocal eyeglasses, novel lens eyeglasses, various contact lens therapies, orthokeratology, and muscarinic antagonists such as atropine and pirenzepine.^[14,15]^ However, it is reported that none of the spectacle lenses had any significant effect in slowing the progression of myopia. Gas permeable contact lenses have been shown to slow the progression of myopia, but the low incidence of microbial keratitis should not be dismissed, especially in children. The pharmacological treatment has been reported to be associated with adverse effects, including pupil dilation and temporary paralysis of accommodation.^[16–19]^ Consequently, this reality drives us to search for additional effective and low-risk interventions of treatment for myopia.

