### Study design

2.2

This clinical study is a parallel-group, randomized controlled, and single-blind study. The experiment will begin in August 2020 and will be completed in August 2023. After obtaining informed consent, 300 eligible adolescents will be recruited and randomly divided into acupuncture Deqi group, acupuncture without Deqi group, and waiting list group. The trial will include a 3-month treatment period and a 9-month follow-up period. All groups will be given frame glasses for corrective treatment; patients in the acupuncture Deqi group will also be treated with acupuncture at acupoints around the eyes to Deqi, while acupuncture without Deqi group will be treated with acupuncture, but no needle manipulation will be performed. The waiting list group will not receive acupuncture treatment. Results will be assessed at 3 points, including baseline, end of acupuncture treatment, and end of follow-up (Fig. 1 flowchart and Fig. 2 visit indicators). The purpose of this study is to objectively evaluate the clinical efficacy of acupuncture at 3 acupoints (Sizhukong, Tongziliao, and Sibai) in adolescents with myopia. All patients will be required to complete written informed consent before enrolment. If patients are unable to complete written informed consent, it will be obtained from their relatives.

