### Exclusion criteria

2.7

Patients meeting any of the following criteria will be excluded from the study:

(1)Patients age <7 years or >16 years, patients not suffering from myopia, or patients with myopia and strabismus/amblyopia;(2)myopia related to retinal dystrophies or collagen syndromes, and developmental disorders;(3)subjects with serious systemic diseases, such as cerebrovascular, liver, kidney, hematopoietic system, and psychiatric diseases;(4)use other related drugs or treatments within 2 weeks;(5)Spherical equivalent (SE) < -0.5D, or combined with pathologic myopia-related fundus changes and/or significant visual function impairment;(6)the affected eyes have other diseases that affect the determination of acupuncture efficacy;(7)patients with less than 14 weeks of follow-up, inability to obtain refraction data in the first 14 weeks, patients lost to follow-up, or unable to keep office follow-up at our institution.

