### Sample size

2.9

This study is a RCT, and the diopter of the research object is the main observed outcome index. According to previous literature reports, it is estimated that the mean diopter of experimental group 1 is -1.52, the standard deviation is 0.87, and the diopter of experimental group 2 is- 1.81, the standard deviation is 1.25. Set α = 0.25 (2-sided) and β = 0.10. We use PASS 15 software (PASS 15.0.5 NCSS, LLC USA) to calculate the experimental size of the test group and the control group N1 = N2 = N3 = 74 cases. Assuming that the loss to follow-up rate of the study subjects is 20%, the sample size is N1 = N2 =  = N3 = 74÷0.8 = 93 cases. Therefore, the minimum sample size included in this study is 279 cases. In the actual study, a total of 300 cases will be included.

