#### Primary outcome

2.12.5

The primary outcome will be diopter measurement of the patients before treatment, 1, 2, 3 months after treatment, and follow-up for 6 , 9 , and 12 months.

Full cycloplegia was obtained 45 minutes after administration of 1% cyclopentolate eye drops (15 mL; Alcon-Couvreur, Puurs, Belgium); Subsequently, the objective optometry (computer optometry and retinoscopy) was measured with a Topcon auto refractor KR8900 (Topcon, Tokyo, Japan); and then subjective optometrics. Subjective optometrics will be divided into the following 2 parts: optometrics will be conducted on a single eye (the right eye followed by the left eye), and a bilateral eye balance examination. Subjective optometrics of a single eye will be divided into the following 3 stages: the initial maximum plus the maximum visual acuity (MPMVA) will be identified, Jackson cross cylindrical lenses will be used to determine the axial direction and degree of the cylindrical lens, and the MPMVA will be repeated. The results will be recorded after optometrics. When the pupils recover, a re-examination will be carried out (3 days after the use of cyclopentolate hydrochloride eye drops). After re-examination, the glasses will be tried again. The degree of the glasses will be marked on the glass trial frame, to be chosen by the subjects based on subjective judgment. Finally, the diopter of the glasses and prescription glasses will be determined. The optometrist will not participate in other parts of the trial.

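### Carrying the last refraction forward assumes that myopia stops progressing at dropout, which could create a spurious difference between arms if dropout is unequal and dilutes a growing effect if it is equal

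*Protocol article*

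**What the plan says.** Section 2.16 (Statistical analyses) defines the full analysis set as everyone randomised and then states "On the basis of rule of the last-observation-carried-forward, missing values will be imputed". No other missing-data rule appears, no reason is given, and the rule is not confined to a sensitivity analysis. The same section plans a repeated-measures ANOVA across the three groups and pairwise tests based on "time-intervention interactions in the mixed-effect models". It also runs the analyses in a per-protocol set of completers.

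The rule will be used. Section 2.9 (Sample size) plans for 20% loss ("Assuming that the loss to follow-up rate of the study subjects is 20", in per cent), and section 2.8 (Informed consent) keeps the data of withdrawn participants for the final analyses.

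On the outcome, section 2.12.5 says "The primary outcome will be diopter measurement of the patients before treatment, 1, 2, 3 months after treatment", and then lists months 6, 9 and 12. Section 2.2 (Study design) says "The trial will include a 3-month treatment period and a 9-month follow-up period". The participants are 7 to 16 years old (section 2.6). The Introduction describes the therapeutic aim in terms of progression: "There has been an increase in efforts to slow the progression of myopia".

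**The concern.** Carrying the last value forward assumes that nothing changes after the last visit. That is hard to defend for refraction in myopic children. A child last seen at month 3 would be recorded as stable for the remaining nine months, and stability is the very benefit a treatment would have to show.

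Two consequences follow. First, if one arm loses more children, or loses them earlier, more of its progression is erased and its mean looks less myopic. This happens even when treatment does nothing and dropout is unrelated to outcome. Secondly, if dropout is the same in both arms, the erased progression cancels, but a true effect that grows with time is cut short in every dropout and so is underestimated.

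Unequal dropout is plausible because the arms differ visibly. Two arms are needled, and section 2.14 lists possible harms such as pain, bleeding and fainting. For the third, "The waiting list group will not receive acupuncture treatment". The planned contrast of acupuncture without Deqi against waiting list is the one most exposed.

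**Working it through.** **Inputs from the protocol article**
- Planned difference (section 2.9): 1.81 − 1.52 = 0.29 D.
- Planned loss (section 2.9): 20%. The inflation step reproduces: 74 / 0.8 = 92.5, rounded up to 93 per group, and 3 × 93 = 279. The derivation of the 74 is a separate matter and does not enter here.
- Follow-up: 12 months, of which 9 come after treatment ends (section 2.2).
- At 20% loss among 300 children, 0.20 × 300 = 60 would need a carried-forward month-12 value.

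**Assumptions, because the document gives no figure**
- Progression g: 0.25 to 1.0 D/year, linear.
- Dropout by arm, pA and pB, and month of last visit t.

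**Spurious difference at month 12 with no true effect**

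Each dropout loses g × (12 − t)/12 of progression. With the same t in both arms:

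bias = g × (12 − t)/12 × (pA − pB)

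With t = 3, the fraction frozen is 9/12 = 0.75.

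| g (D/year) | 10-point difference | share of 0.29 D | 20-point difference | share of 0.29 D |
|---|---|---|---|---|
| 0.25 | 0.25 × 0.75 × 0.10 = 0.019 | 6% | 0.25 × 0.75 × 0.20 = 0.0375 | 13% |
| 0.5 | 0.0375 | 13% | 0.075 | 26% |
| 1.0 | 0.075 | 26% | 0.15 | 52% |

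Timing matters. At 0.5 D/year and 10 points, a last visit at month 6 gives 0.5 × 0.5 × 0.10 = 0.025 D, and one at month 9 gives 0.5 × 0.25 × 0.10 = 0.0125 D. A last visit at baseline gives 0.05 D.

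A difference in timing alone is enough. With 20% lost in each arm, at month 3 in one and month 9 in the other, the bias at 0.5 D/year is 0.5 × 0.20 × (9 − 3)/12 = 0.05 D.

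**Dilution with equal dropout**

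A true 0.29 D difference that builds up linearly, with 20% lost in both arms at month t, becomes 0.29 × [1 − 0.20 × (12 − t)/12]. This gives 0.232 D for t = 0, 0.247 D for t = 3 and 0.276 D for t = 9.

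**Simulation of the false-positive rate**

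Two arms of 100, no true effect, 3000 runs, dropout unrelated to outcome, and last visits spread evenly over months 0 to 9. Slope SD 0.4 D/year and measurement SD 0.15 D are assumed. The test is a t test on month-12 change at 0.05 two-sided.

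| Dropout | g (D/year) | Spurious difference (D) | Type I error with carry-forward |
|---|---|---|---|
| 20% v 20% | 0.5 to 1.0 | about 0 | about 5% |
| 25% v 15% | 0.5 / 0.75 / 1.0 | 0.036 / 0.053 / 0.071 | 8% / 13% / 16% |
| 30% v 10% | 0.5 / 0.75 / 1.0 | 0.071 / 0.106 / 0.142 | 20% / 36% / 50% |

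Using only observed month-12 values, as a stand-in for a mixed model when dropout is unrelated to outcome, the bias was about 0 and the type I error 4% to 6% throughout.

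**The case against.** **Nothing in the document predicts unequal dropout.** Section 2.9 uses one 20% rate for all groups. Section 2.12.4 gives waiting-list children eye examinations without charge during observation and a free course of acupuncture afterwards, which is a reason to stay. A reader might infer that the waiting list will lose more children, or that dropout is unlikely to be equal. The document supports neither. This stands: the size and direction of the bias are unknown. It does not rescue the rule, which also dilutes a growing effect when dropout is equal.

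**The size depends on the scenario.** No single primary time point is fixed. At month 3, a child last seen at month 1 is frozen for only two months, which gives at most 1.0 × 2/12 × 0.10 = 0.017 D for a 10-point difference. A 20-point gap around a 20% average is extreme. The 0.29 D is stated for two experimental groups, most naturally the needled arms, so for the waiting-list contrast it is only a yardstick. The formula also describes a month-12 mean difference, not the planned time-by-intervention test. All of this stands, so the figures are illustrative.

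**A partial check exists.** The per-protocol completers are largely free of carried-forward values. But completers may be a selected group, so they cannot stand in for a sound analysis of everyone randomised.

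**Exclusion criterion 7 might remove early dropouts.** Section 2.7 lists patients with under 14 weeks of follow-up or lost to follow-up. Applied after randomisation, it would contradict the all-randomised set in section 2.16. If it covered only the first 14 weeks, later dropouts would still be carried forward.

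**Conclusion.** The point holds in conditional form. The protocol fixes an imputation rule that assumes no progression after dropout in a condition it treats as progressive, and it gives no justification. With dropout unequal in amount or timing, the arm losing more or earlier children is shifted towards looking less myopic. With equal dropout, there is no spurious difference but a growing effect is diluted, from 0.29 D to between 0.23 and 0.28 D at 20% loss.

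The criticism of the rule is secure. The size rests on assumed progression rates, dropout by arm and dropout timing, and it ranges from negligible to about half the planned difference.

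Two stronger readings are not supported. One is that the arm with more dropout will look better whatever the treatment does. The bias adds to any true effect, and a shift of 0.02 to 0.15 D would not reverse a true 0.29 D. The other is that the rule makes standard errors too small. In the simulation, the type I error stayed at about 5% with equal dropout, so the excess errors come from the shifted mean.

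**What to change.** In section 2.16:
1. Delete carry-forward as the primary missing-data rule.
2. Make the mixed-effect model already planned the primary analysis. Use all observed visits of all randomised participants, with visit as a category and a group-by-visit term, and state the missing-at-random assumption.
3. Use the same model for the three-group comparison in place of the repeated-measures ANOVA. Without imputation, that ANOVA would fall back to children with complete visits.
4. Add one sensitivity analysis for data not missing at random, for example multiple imputation with a delta adjustment for progression after dropout. Its details can sit in the statistical analysis plan.

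The cost is a short text change and a little more analysis work. Design, visits and sample size are unaffected.

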### Blinding

2.11

This study uses a single-blind method. Acupuncture and acupuncture pseudo-acupoints will be performed by the same professional acupuncturist in the outpatient department according to uniform standards. All examinations will be checked and evaluated by the same doctor. The subjects will not know the specific grouping situation. Outcome evaluation and data statistics are performed by a third party who is not involved in the treatment. Only in emergency situations, such as a serious adverse event (AE), or when the subject needs emergency rescue, the researcher will report to the supervisor and the principal investigator to decide whether to unblind. Once the subject is unblinded, the case will be regarded as a drop-out case and will not be included in the efficacy analysis. However, if there is an adverse reaction, it should be included in the adverse reaction analysis, and the unblinding should be recorded in the Case Report Forms (CRFs) “Early Subject Exit Page” Related information, including the time of unblindness, reason, treatment, and treatment status.

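### Safety is to be analysed on a completers-only per-protocol set beside the full analysis set, with no statement of which governs

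*Protocol article*

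**What the plan says.** Section 2.16 (Statistical analyses) defines two sets. The FAS is every randomised participant, on the intention-to-treat principle. The PPS "is for the individuals who complete the trial and do not have significant protocol violations". The section then assigns both sets to both purposes: "In order to evaluate therapeutic effect and safety, the FAS and PPS will be used simultaneously". It names no other set for safety and does not say which of the two governs if they differ.

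Section 2.11 (Blinding) deals with children unblinded in an emergency, for example after a serious adverse event: "Once the subject is unblinded, the case will be regarded as a drop-out case and will not be included in the efficacy analysis". It continues: "However, if there is an adverse reaction, it should be included in the adverse reaction analysis".

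Section 2.14 (Safety evaluation) has adverse events recorded for the whole of the study. It lists the harms expected from needling, among them bleeding, hematoma, fainting and local infection.

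**The concern.** A set restricted to children who finish the trial selects on something that harm can cause. If a child faints or develops a local infection and leaves for that reason, the event disappears from the PPS because it was bad enough to end participation. Events of that kind have a PPS rate of zero by construction, whatever their true frequency.

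This is a rule the article states, not a detail it leaves to a later plan: it assigns the PPS to safety.

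The participants are aged 7 to 16, and the Discussion says the trial should supply evidence on the safety of acupuncture with Deqi. With two safety analyses and no ranking, a report could lean on the lower rate. The comparison between arms can be affected too. Waiting-list children are not needled during the study (section 2.12.4), so withdrawal caused by needling can arise only in the two acupuncture arms. Where it does, the PPS comparison with the waiting list is pulled towards no difference in harm.

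**Working it through.** **Which children each set keeps**

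| Child | FAS | PPS |
|---|---|---|
| Completes, no significant violation, has an event | counted | counted |
| Leaves the trial because of an event | counted | absent |
| Unblinded after an event, classed as a drop-out (2.11) | counted | absent |
| Stops needling after an event but attends all visits | counted | depends on whether stopping is a significant violation; not stated |

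**Inputs**

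- Children per arm: 300 in total at 1:1:1 (sections 2.9 and 2.10), so N = 300/3 = 100.
- Loss: 20% (section 2.9), so E = 0.20 × 100 = 20 children outside the PPS. This assumes that all losses, and nobody else, are excluded.
- Children with an event: the article gives no rate. A = 10 per arm is assumed, and 5 and 20 are tried below.
- Children with an event among the excluded: x, also not given, so the range is shown.

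The plan states no safety rate to reproduce. Its use of the 20% does reproduce: 74/0.8 = 92.5, rounded up to 93, and 3 × 93 = 279.

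**Formulas**

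FAS rate = A/N. PPS rate = (A − x)/(N − E).

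The PPS rate is the lower of the two when (A − x)/(N − E) < A/N, which simplifies to x/E > A/N. In words, events must be more frequent among excluded children than overall. The break-even is x = E × A/N.

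**Results for A = 10 (FAS rate 10/100 = 10%)**

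Break-even: 20 × 10/100 = 2.

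| Excluded children with an event | PPS rate |
|---|---|
| 0 | 10/80 = 12.5% |
| 1 | 9/80 = 11.25% |
| 2 | 8/80 = 10% |
| 5 | 5/80 = 6.25% |
| 10 | 0/80 = 0% |

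**Other assumed event rates**

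- A = 5 (FAS 5%): break-even 20 × 5/100 = 1. With 2 of the 5 excluded, the PPS rate is 3/80 = 3.75%.
- A = 20 (FAS 20%): break-even 20 × 20/100 = 4. With 10 of the 20 excluded, the PPS rate is 10/80 = 12.5%.

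**The case against.** The strongest reply is that nothing is lost. The FAS is also used for safety, it holds every randomised child, and events are recorded throughout. A child who leaves after an event is therefore counted in one of the two planned analyses, and the PPS merely adds a weaker table. This stands, and it limits the point: the plan does not evaluate safety on completers alone. It does not make the added table a valid estimate of harm, and the article does not say that the FAS takes precedence.

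Three stronger readings are tempting, but the documents do not support them.

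- A reader might infer that sections 2.11 and 2.16 contradict each other, since a drop-out cannot belong to a completers' set. Section 2.11 asks only that the reaction be in the adverse reaction analysis, and the FAS analysis can meet that. It does not require the reaction to appear in every tabulation. If anything, it shows an intention to keep these events.
- A reader might infer that the PPS always understates harm. It does so only above the break-even. If excluded children had few events, the PPS rate would be too high. Nor does every child who stops needling leave the PPS: section 2.14 provides for close follow-up of mild and moderate events, and such a child may complete the trial.
- A reader might infer that the FAS is itself unsound for safety because it groups children as randomised. The documents give no sign of crossover, and waiting-list children are offered acupuncture only once the study is complete.

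It is also fair to say that a separate safety set is often defined in a statistical analysis plan, so its absence from an article is not a fault. The point here is the opposite: a set unsuited to safety is named for it.

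**Conclusion.** The point holds in limited form. Section 2.16 commits the trial to a safety analysis from which any event that ends a child's participation is missing, and does not rank it below the FAS analysis that includes such events. The consequence is one potentially misleading safety result beside a sound one, not the loss of safety data.

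The size cannot be fixed from the article, which gives neither an event rate nor the share of events leading to exit. With 100 per arm, 20 excluded and 10 children with an event, a full rate of 10% could appear in the PPS as anything from 0% to 12.5%. It is too low when more than 2 of the 20 excluded children had an event. The case to worry about is withdrawal linked to harm, where the error runs towards understatement.

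This takes the FAS at its stated definition of all randomised children.

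**What to change.** In section 2.16, confine the PPS to efficacy. State that safety is analysed on all participants, including drop-outs and unblinded cases, with needled children grouped by the treatment they received and waiting-list children as observed. A cross-reference to the rule in section 2.11 would make clear that adverse reactions in unblinded children belong to this analysis.

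The cost is one sentence and no new data. The downside for the sponsor is that reported adverse event rates may look slightly less favourable than a completers' table would.

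### The three-group repeated-measures ANOVA names neither the tested term nor the role of baseline: one reading loses power, and the other can exceed 5% if left uncorrected

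*Protocol article*

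**What the plan says.** Section 2.16 (Statistical analyses) gives the three-arm comparison one sentence: "Repeated-measures ANOVA will be used to compare the intergroup differences among the 3 groups". It does not say whether the group main effect or the group-by-visit interaction is meant, which visits enter, or whether baseline is a repeated level or a covariate. Sphericity is not mentioned. The general criterion is a P "value of less than .05 (2-sided) indicates a statistically significant difference".

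Two pairwise comparisons, Deqi versus without Deqi and without Deqi versus waiting list, go to a different analysis, "based on time-intervention interactions in the mixed-effect models". Deqi versus waiting list is not among them, so the ANOVA is the only stated between-group analysis that covers it. On missing data, "On the basis of rule of the last-observation-carried-forward, missing values will be imputed". On software, "Data analyses will be processed with SPSS 22.0".

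Section 2.12.5 defines the outcome: "The primary outcome will be diopter measurement of the patients before treatment, 1, 2, 3 months after treatment", followed by months 6, 9 and 12. That makes seven visits, one of them before treatment. Section 2.15 agrees on the six later visits: participants are "assessed at the first, second, third, sixth, ninth, and twelfth months after recruitment". Section 2.2 instead has results assessed at three points: baseline, end of treatment and end of follow-up.

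**The concern.** The sentence allows two tests, and each has its own weakness.

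- **Group main effect.** This compares the arms on each child's average over the visits. If the visits listed in section 2.12.5 all enter, a value that cannot carry a treatment effect is averaged in. The permanent differences in refraction between children also stay in the error term, although the baseline measurement that could remove most of them has been collected.
- **Group-by-visit interaction.** This removes the permanent differences, but the univariate F keeps its 5% level only under sphericity, meaning equal variance of all between-visit differences. If children progress at different rates, the difference between months 0 and 12 varies more than the difference between months 1 and 2.

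At stake is the only three-arm test in the plan, and with it the only stated comparison of Deqi with the waiting list.

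**Working it through.** **Inputs from the article.** Visits at months 0, 1, 2, 3, 6, 9 and 12 (2.12.5); 300 children allocated 1:1:1, so 100 per arm (2.9, 2.10); planning difference 1.81 - 1.52 = 0.29 D with SDs 0.87 and 1.25 (2.9), root mean square √((0.87² + 1.25²)/2) = 1.077. The article states no error rate for the ANOVA except the nominal .05, so there is no other figure to reproduce.

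**Assumptions.** The article gives no within-child variance. I use a random-intercept SD of 1.05 D, a slope SD b of 0 to 0.6 D per year and a visit-error SD s of 0.15 or 0.25 D. Serial correlation of 0.90 to 0.98 per month is the alternative. No dropout is assumed.

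**1. Main effect: share of the effect kept**
- Constant from month 1: 6/7 = 0.857, so 0.29 D becomes 0.249 D.
- Linear to month 12: (0+1+2+3+6+9+12)/(7×12) = 33/84 = 0.393, so 0.29 D becomes 0.114 D.

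**2. Main effect: power, worked at b = 0.3, s = 0.25**
- Seven-visit mean: variance 1.05² + 0.3²×0.393² + 0.25²/7 = 1.125, SD 1.061. SE of a pairwise difference = 1.061×√(2/100) = 0.150. The ratio 0.249/0.150 = 1.66 gives power of about 38%. For the linear profile, 0.114/0.150 = 0.76 gives about 12%.
- Mean of the six post-baseline visits (mean time 33/72 = 0.458 years): variance 1.05² + 0.3²×0.458² + 0.25²/6 = 1.132, SE 0.150, power about 48%.
- The same mean with baseline as covariate: baseline variance 1.1025 + 0.0625 = 1.165, covariance 1.1025, residual variance 1.132 - 1.1025²/1.165 = 0.088. SE = √(2×0.088/100) = 0.042, ratio 6.9, power over 99%.
- Month 12 alone with baseline as covariate: residual variance 1.1025 + 0.09 + 0.0625 - 1.043 = 0.212, SE 0.065, ratio 4.5, power about 99%.

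Across the random-slope settings checked, power is 37-39% for the seven-visit mean and 47-50% for the post-baseline mean.

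Under pure serial correlation the covariate helps less. At month 12 the residual SD is 1.05×√(1 - 0.98²⁴) = 0.65 at 0.98 per month (power about 88%) and 1.05×√(1 - 0.90²⁴) = 1.01 at 0.90 per month (about 53%).

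**3. Group-by-visit: type I error without correction**

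The variance of a between-visit difference is b²(t_j - t_k)² + 2s². At b = 0.4, s = 0.15 this is 0.16 + 0.045 = 0.205 for months 0 to 12, and 0.16/144 + 0.045 = 0.046 for months 1 to 2. By Box's approximation, the F with (12, 1782) df behaves as F(12ε, 1782ε), where 1782 = 6×(300 - 3).

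| b | s | ε, 7 visits | Type I, 7 visits | Type I, 3 points |
|---|---|---|---|---|
| 0 | 0.15 | 1.00 | 5.0% | 5.0% |
| 0.2 | 0.25 | 0.97 | 5.2% | 5.1% |
| 0.3 | 0.25 | 0.88 | 6.0% | 5.5% |
| 0.4 | 0.25 | 0.75 | 7.2% | 6.0% |
| 0.3 | 0.15 | 0.61 | 8.8% | 6.5% |
| 0.4 | 0.15 | 0.45 | 11.4% | 7.3% |
| 0.6 | 0.15 | 0.30 | 14.4% | 8.2% |

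Serial correlation of 0.90 to 0.98 per month gives 11-13% with seven visits. The ceiling, at ε = 1/6, is 17.4%. Null simulations agree with these values. With the Greenhouse-Geisser correction, simulated rates are 4.5% to 6.2% in every seven-visit setting (simulation SE about 0.35 points).

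**4. Carrying values forward does not restore sphericity.** With 20% dropout equal across arms, at b = 0.3 and s = 0.15, the simulated rate was 9.3% against 8.8% without dropout, a change within simulation error.

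**The case against.** The strongest reply is that this is a condensed article. It nowhere says that no correction is made, an epsilon correction is ordinary analysis-plan detail, and the SPSS repeated-measures procedure normally prints corrected rows beside the uncorrected one. That stands: a reader might infer that the plan has decided against a correction, but silence is not a decision.

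Four other strong readings also fail.

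- Inflation well above 5% is not established. It depends on covariances the article does not give, and mild settings stay at 5-6%. Neither a changing mean nor uneven spacing breaks sphericity by itself; spread in progression rates or serial correlation does.
- The main-effect P value is not invalid. Averaging in baseline costs power only.
- That baseline enters as a repeated level is an inference from the visit list in section 2.12.5; section 2.16 does not say so.
- The main aims do not hang on this test. The Discussion frames them as two contrasts, both assigned to mixed models, and no passage makes the three-arm test primary or a gatekeeper.

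What remains is that the article does fix the method for the three-arm comparison, and that no sphericity correction cures the loss of power on the main-effect reading. The planned mixed models do not supply Deqi versus waiting list, although the Discussion also refers to the overall effect of acupuncture with Deqi.

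**Conclusion.** The point holds in a conditional form. On the main-effect reading over the listed visits the test is valid but weak: about 38% pairwise power for a constant 0.29 D and about 12% for an effect reaching 0.29 D at month 12, with 100 per arm. On the group-by-visit reading, and only if uncorrected, type I error runs from about 5-6% in mild settings to 8-13% when progression rates vary strongly relative to measurement error. It reached 14.4% at the most extreme setting tried, and at most about 8% in the same settings with three time points.

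The type I figures rest on assumed within-child covariances, as does the size of the gain from adjusting for baseline. The 6/7 and 39% shares rest only on the listed visits and the assumed shape of the effect. The power gain is measured against the main-effect reading; the interaction test already removes permanent differences between children.

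**What to change.** In section 2.16, replace the repeated-measures ANOVA with one three-arm mixed model for repeated measures: post-baseline diopter as response, pre-treatment diopter as covariate, visit as a categorical factor and an unstructured within-child covariance. Take the three-arm test and all pairwise contrasts from it, including Deqi versus waiting list, and name the term or visit at which each is read. This extends a model family the article already plans, and SPSS can fit it. The model uses the observed visits, so the carry-forward rule should be reworded for this analysis.

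If the ANOVA is kept, state that the Greenhouse-Geisser-corrected group-by-visit P value is the one used.

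Reconcile the three assessment points of section 2.2 with the visits in sections 2.12.5 and 2.15, so that the visits entering the model are fixed.

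The cost is wording, plus 6×7/2 = 21 covariance parameters for six post-baseline visits, which 300 children support. No extra data are needed.
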